### Criteria for discontinuing or modifying allocated interventions {11b}

In the case of any adverse event (AE) or serious adverse event (SAE), the study therapist immediately informs the physician (from the rehabilitation center at T0 and T1, or from the follow-up center at T2 and T3). The review of the situation and decision to stop the intervention will be taken according to the physician’s judgment. Within 1 week, the study therapist will inform the study coordinator as well in order to document the event.

In the study, an adverse event is classified as follows:
Unintentional illness or injuryAdverse clinical observation (including abnormal laboratory results)

A serious adverse event is defined as a health impairment that:
Leads to death (during the study or up to four weeks after the end of the study)Is life-threateningLeads to a permanent or temporarily significant disability/impairmentLeads to hospital admission (> 24 h) or extension of an existing hospital stayIs a congenital anomaly or birth defect (in descendants of patients)

Beyond, the patient can withdraw their informed consent at any time resulting in discontinuation of intervention. Furthermore, the change of randomized allocated intervention at T0 (from intervention to control group and vice versa) is exclusively possible as a result of an explicit patient request, and only after a detailed conversation about the benefits of the assigned intervention. Moreover, control group patients are offered access to a part of study materials, after completing their participation.

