## Assignment of interventions: blinding

### Who will be blinded {17a}

Open trial, neither participants, intervention instructors, nor outcome assessors are blinded to the group assignment.

However, participants do not receive information about the study objectives, regarding whether they receive the novel intervention studied. Furthermore, the instructors do not inform participants about their risk classification and the meaning of the individualized intervention modules.

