## Statistical methods

### Statistical methods for primary and secondary outcomes {20a}

Data is analyzed at the end after T3 data collection completion. Then, an examination of underlying assumptions for parametric or non-parametric hypothesis testing is applied. For the primary outcome pain (DISS, CPI), an analysis of variance (ANOVA) repeated measures for three time points (T0, T2, T3) between the groups (intervention vs control group) with covariates adjustment is planned. The covariates to include in the analysis are center, age, and sex. A complete case analysis is intended.

For secondary outcomes (psychometric items), missing value imputation follows only (in case of psychometric scores) the specific test manuals. Likewise, variance analytical testing is proposed. A sensitivity analysis is planned for concomitant therapy, such as medications.

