### Methods in analysis to handle protocol non-adherence and any statistical methods to handle missing data {20c}

Intention to treat analysis will be performed. Per-protocol analysis is going to be applied to compare the results in a sensitivity analysis.

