### Adverse event reporting and harms {22}

The contact persons in case of such an event are both the study therapist and the corresponding physician in the clinic during the center-based phase (T0–T1) or the physician in the respective follow-up center (T2–T3). If the study therapist has been informed first about the adverse event, he/she immediately informs the physician. It is always the treating physician who decides whether to exclude the patient from the study.

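### An adverse event may end the intervention in one section and study participation in another, which under complete-case analysis can remove randomised patients; separately, arm changes on request at T0 dilute an effect powered for dropout only

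*Protocol article*

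**What the plan says.** All places are in the protocol article.

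- **Adverse events, section {11b}:** "The review of the situation and decision to stop the intervention will be taken according to the physician’s judgment". The decision concerns the intervention.
- **Adverse events, section {22}:** "It is always the treating physician who decides whether to exclude the patient from the study". The decision concerns the study.
- **Change of arm, section {11b}:** "the change of randomized allocated intervention at T0 (from intervention to control group and vice versa) is exclusively possible as a result". The trigger named there is the patient's own express wish, following a talk about what the assigned programme offers. Both directions are allowed. The same section gives controls part of the study materials once they have finished participation.
- **Analysis set, section {20c}:** "Intention to treat analysis will be performed", with a per-protocol analysis for comparison.
- **Missing outcomes, section {20a}:** "A complete case analysis is intended" for the primary repeated-measures ANOVA over T0, T2 and T3.
- **Blinding, section {17a}:** "neither participants, intervention instructors, nor outcome assessors are blinded to the group assignment".
- **Sample size, section {14}:** d = 0.2, alpha 5%, power 80%, 1:2 allocation, three time points, correlation 0.57, 843 evaluable, and 30% dropout giving 1204. Dropout is the only loss allowed for.

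**The concern.** Two mechanisms are involved, and they do different harm.

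**Exclusion.** Stopping a programme and leaving the study are different acts. After the first, the patient can still be surveyed at T2 and T3. After the second, those surveys may never happen, and a complete-case analysis then omits the patient. The decision falls after randomisation, is made without blinding, and follows an illness, injury or adverse clinical observation, some of which will bear on pain and disability. If exclusions differ between arms, the comparison is biased, and a larger sample does not cure that.

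**Arm changes.** A written route into the other arm's programme reduces the contrast between the arms. Patients may have a reason to use it: the section on the control group says that a patient who cannot attend a centre receives no aftercare, whereas the intervention is done at home. With a planned effect of only 0.2 SD, there is little to give away.

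**Working it through.** **1. Exclusion: the sections side by side**

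- {11b}: adverse event, then the physician decides on the intervention.
- {22}: adverse event, then the treating physician decides on study membership.
- {20a}: complete cases over T0, T2 and T3.
- {20c}: intention to treat.

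If exclusion under {22} ends the surveys, the patient has no T2 or T3 score, fails the condition in {20a}, and is missing from the comparison named in {20c}. Neither section says that surveys continue after exclusion.

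The documents give no exclusion rate, so the size can only be illustrated. If one arm loses an extra fraction e of patients, whose mean score would have differed by δ SD from those who stay, that arm's mean is biased by e × δ.

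| e (assumed) | δ (assumed) | Bias, SD |
|---|---|---|
| 2% | 0.5 | 0.010 |
| 5% | 0.5 | 0.025 |
| 5% | 1.0 | 0.050 |
| 10% | 1.0 | 0.100 |

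Against a planned 0.2 SD, 0.025 is one eighth and 0.100 is one half.

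**2. Arm changes: the plan's own figure first**

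For the between-groups effect in a repeated-measures ANOVA, power comes from a noncentral F with 1 and N − 2 degrees of freedom and

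λ = f² × N × m / (1 + (m − 1)ρ), with m = 3 and ρ = 0.57, so the divisor is 2.14.

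- For 1:2 allocation, f² = d² × (1/3)(2/3) = 0.04 × 2/9 = 0.00889. Power of 80% needs N = 632, not 843.
- For equal groups, f² = (d/2)² = 0.01 and 80% needs N = 562. The article prints 562 as the intervention arm, and 562 + 281 = 843. The equal-groups total may have been taken as the intervention arm; this is an inference.
- The printed arms, 562 and 289, sum to 851. I use 562 and 281.
- 843 / 0.7 = 1204.3, so 1204 follows from 843.
- At N = 843 with 1:2 allocation, λ = 0.00889 × 843 × 3 / 2.14 = 10.50 and power is 89.9%.

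There are therefore two starting points: the stated 80%, and 89.9% on the protocol's own model at 843.

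**3. Dilution**

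Assume that a fraction s of each arm swaps and that swappers get the full effect of the programme they receive. Then d = 0.2 × (1 − 2s).

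- From the stated 80%: power = Φ((1.96 + 0.8416)(1 − 2s) − 1.96).
- On the between-groups model: the formula in step 2 with the reduced d and N = 843.
- For a plain comparison at T2, the main time point: power = Φ(d / √(1/562 + 1/281) − 1.96).

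| s, each arm | d | From stated 80% | Between-groups model, 843 | T2 only, unadjusted |
|---|---|---|---|---|
| 0 | 0.200 | 80% | 89.9% | 78% |
| 1% | 0.196 | 78% | 88.7% | 77% |
| 5% | 0.180 | 71% | 83.0% | 69% |
| 10% | 0.160 | 61% | 73.6% | 59% |

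On the between-groups model, power drops below 80% at about 6.7% each way. For scale, 5% of each arm is about 60 of 1204 patients (0.05 × 1204 = 60.2).

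The 89.9% is itself model-dependent. It takes 0.2 as the group difference averaged over T0, T2 and T3, but randomisation implies no difference at T0. If 0.2 applies only at T2 and T3, the average is 0.2 × 2/3 = 0.133, and the same formula gives 58% before any swap.

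**The case against.** A reader might infer that the swap rule breaks randomisation. The documents do not support that. Section {20c} names intention to treat, which means analysis as randomised; an as-treated primary analysis is not planned. Dilution pulls the estimate towards no difference in a superiority trial, which costs power but not validity. This objection stands.

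A reader might also infer that a small number of swaps ruins the power. That is not shown. No rate is given, the rule is restricted (T0 only, explicit request, after a conversation), and 1% each way costs under two percentage points. The figures 71% and 61% depend on accepting the stated 80%. This stands too, which is why both starting points are shown. The calculation also assumes equal swap fractions and full crossover of effect.

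On exclusion, section {22} does not say that surveys stop, many adverse events will have nothing to do with treatment or outcome, and no figure shows unequal exclusion. A biased result is therefore a possibility that the wording leaves open, not an established consequence. The conflict between {11b} and {22} remains.

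Finally, the trial is pragmatic and allows concomitant care, so forbidding swaps would not stop intervention patients from using standard aftercare. That limits what the fix achieves but does not remove the case for it.

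**Conclusion.** The point holds in two parts of unequal weight.

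The firmer part is the conflict between {11b} and {22}. Read with the complete-case rule, it lets an unblinded decision after randomisation take patients out of the intention-to-treat comparison. The bias cannot be sized from the documents. It depends on how many patients are excluded, how they differ from the rest, and whether the arms differ in this.

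The second part is a loss of power, not of validity. Under equal swapping with full crossover of effect, 5% each way costs 7 to 9 percentage points and 10% each way costs 16 to 19, depending on the starting point. The sample size has no allowance for this. Whether power ends below 80% depends on the unknown swap rate and on which model describes the analysis.

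Both parts concern rules of conduct that the protocol itself sets. An analysis plan cannot recover outcomes that were never collected. This is a cheap improvement worth making, not a fatal flaw.

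**What to change.** 1. Reconcile {11b} and {22} so that ending the intervention after an adverse event does not end outcome collection, unless the patient withdraws consent. The physician's clinical decision stays as it is.
2. Replace the offer of the other arm's programme with the option to decline or leave the assigned one. This mainly closes the route from control to intervention, since intervention patients can still use standard aftercare. It also fits the existing rule that controls get study materials only after completing participation.
3. State that every patient, including any who have already swapped, keeps the randomised arm for the T1 to T3 surveys and for the primary analysis.
4. Report swaps and exclusions by arm. A complier-average sensitivity analysis is optional.

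The cost is protocol wording and therapist instruction. Two drawbacks should be accepted openly: a few patients with strong preferences may withdraw instead of swapping, and a participant-facing rule would change while recruitment is under way.

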### Strategies to improve adherence to interventions {11c}

One of the strategies to improve adherence to the interventions is to schedule training sessions by assigning electronic appointments. This strategy supports the “follow-up adherence,” which refers to the completion of the scheduled assessment measures [30]. The procedure was already successfully tested and implemented in the pilot study (material unpublished), and it will be achieved in the study again with the help of the scheduling department of the rehabilitation clinic.

The study therapist is at the clinic at least 3 days per week and once after the discharge of the last participant. He/she is also available by telephone at fixed times during the first 12 weeks of intervention to support all participants. This strategy intends to reduce misunderstandings about training regimens [30].

Moreover, at the first session, participants in the intervention group receive a training journal and an exercise booklet to improve the adherence to the intervention. Self-reporting diaries are a common measure of adherence in clinical trials [31]. Besides, the training journal is used to monitor adherence and the participant will return it at the end of the follow-up home-based training (T3).

### Relevant concomitant care permitted or prohibited during the trial {11d}

Concomitant care is allowed during the trial.

The trial setting is the rehabilitation clinic and home. Therefore, no broader supervision is possible or intended. The study has a pragmatic approach with the aim of allowing the patient to function in his or her real context. At T0 and T3, the actual medications (prescribed or not prescribed) will be recorded.

### Provisions for post-trial care {30}

No post-trial care is planned.

### Outcomes {12}

#### Risk stratification

##### Risk Stratification Index (RSI) and Risk Prevention Index (RPI-S)

The Risk Stratification Index (RSI) is a screening tool that allows an estimation of the risk of low back pain chronicity (1-year prognosis) through psychosocial risk factors. It includes baseline pain, unhappiness, social support and status, distress (chronic worries), work dissatisfaction, misfortune, pain persistence, sleep problems, and other health care issues such as medication history and insurance status [11].

The Risk Prevention Index (RPI-S) is a screening tool that identifies further individual therapy needs of low back patients, based on the risk within four psychosocial domains (distress, pain experience, social environment, and medical care environment). It also incorporates expectations to exercise treatments [11].

Both screening tools were derived through LASSO (least absolute shrinkage and selection operator) models, which covered yellow, black, and blue flag factors for chronic back pain and disability, as well as demographic and protective factors [32].

#### Primary outcomes

##### Chronic pain

The study has 2 co-primary outcomes (Characteristic Pain Intensity and Disability Score).

*Chronic pain* is assessed by the German version of the Chronic Pain Grade Questionnaire (CPG) [33, 34], which comprises two subscales: characteristic pain intensity (CPI: 0 = “no pain” to 100 = “pain as bad could be”) and disability score (DISS: 0 = “no disability” to 100 = “unable to carry on any activities”) from the past 3 months. Both subscales consist of the mean of three individual Numeric Rating Scales ranging from 0 to 10, showing good internal consistency (Cronbach’s alpha 0.88 and 0.68, respectively, from the literature [34]). Furthermore, these subscales display moderate to high relations to other instruments measuring a patient’s disability. Therefore, the CPG questionnaire is a reliable and valid instrument when an uncomplicated grading of chronic pain severity is required [34]. The CPG is administered at all time points (T0, T1, T2, and T3). The main time point is T2.

#### Secondary outcomes

##### Current pain

Current pain intensity is also assessed before and after functional diagnostics at all time points by the *Numeric Rating Scale* (NRS), which is an 11-point numeric scale ranging from 0 (representing one pain extreme “no pain”) to 10 (representing the other pain extreme “worst pain imaginable”). High test-retest reliability in patients with arthritis has been shown, reporting a Pearson *r* coefficient of 0.96 before and after medical care [35].

The *Brief Pain Inventory* [BPI] [36] includes two subscales: pain severity and pain interference. The first one is the mean of four current pain items (worst, least, average, and now), while  the second one is constructed by the mean of pain interference during seven daily activities (general activity, walking, work, mood, enjoyment of life, relations with others, and sleep) [36]. Cronbach’s alpha is reported to be 0.88 for pain severity and 0.92 for pain interference [37].

##### Functional and work ability

This is defined as work ability, days of incapacity to work, and subjective prognosis of employment.

*Work ability* is measured via the Work Ability Index (WAI) following the 2017 WAI Germany network guideline [38]. This questionnaire comprises seven thematic dimensions. Counting all dimensions, the highest score 49 indicates maximum work ability, while the lowest 7 suggests the opposite. The first dimension assesses the current work ability compared to the best work ability ever accomplished. The second one measures work ability in relation to work demands. The third and fourth dimensions record current illnesses diagnosed and their related impairment on work performance. The fifth dimension collects the number of sick days in the past year (days of incapacity to work). The sixth assesses the ability to work 2 years from now. Finally, the last dimension asks about the mental performance reserves [39]. Cronbach’s alpha (reliability) reported in the literature is 0.83 [40].

*Days of incapacity* to work are recorded in one of the WAI questions (“How many full days did you stay away from work due to a health problem (illness, health care or examination) in the last year (12 months)?”), and it has five categorical answers from none to within 100 and 365 days. Moreover, the rehabilitation report from the study center could confirm this information (days of incapacity to work).

*Subjective prognosis of employment* is characterized by the total score of the subjective prognosis of gainful employment (SPE) questionnaire. The score ranges from 0 to 3, the higher score means a worse prognosis. Internal consistency was confirmed in a cohort study of patients with severe low back pain and is recommended for rehabilitation research [41].

##### Psychometric items

Questions about health-related quality of life (12-Item Short-Form Health Survey: SF-12) [42]; physical activity (International Physical Activity Questionnaire (IPAQ) [43]); subjective well-being regarding stress, moods, fatigue, anxiety, and depression (Trier Inventory for Chronic Stress (TICS) [44], Profile of Mood States (POMS) [45], vital exhaustion (VE) [46], Hospital Anxiety and Depression Scale (HADS) [47]); fear-avoidance beliefs (FABQ-D) [48]; support (Berlin Social Support Scales (BSSS) [27]); and life-changing events (ILE) [49] are recorded.

*SF-12 short form of the Health Survey SF-36* [42]: the questionnaire measures non-disease-specific quality of life. Both scales have values from 0 to 100, higher values indicate a better health-related quality of life. Cronbach’s alpha range from 0.72 to 0.89 [42].

*The International Physical Activity Questionnaire Short Form* [IPAQ] [43]: it measures specific types of physical activity among adults: walking, moderate-intensity, and vigorous-intensity activities. The total score (median and interquartile range) combines the duration and frequency of the physical activity weighted by its energy requirement [50]. Cronbach’s alpha is 0.60 for this short version [51].

The *Trier Inventory for Chronic Stress* [TICS] [44]: the questionnaire encompasses a 3-month observation period. It comprises 57 items with five answers from 0 (“never”) to 4 (“very often”). Ten scales characterize different areas of chronic stress. Workload, social overload, and pressure to succeed scales describe stress related to excessive demands. The scales work dissatisfaction, excessive demands at work, lack of social recognition, social tension, and social isolation measure stress connected to a lack of needs satisfaction. Furthermore, the chronic concern and screening scales serve as a global measure of chronic stress. A Cronbach’s alpha between 0.84 and 0.91 is known from the literature [44].

*Profile of Mood States* [POMS] Short Form, German version [45]: it measures psychological well-being (mood) and includes four scales (depression/anxiety, fatigue, vigor, and irritability) from 35 individual items. Cronbach’s alpha ranges between 0.89 and 0.95 [45].

*Vital exhaustion* [VE] [46]: VE is a measure using a nine-item short-form German version of the original 21-item Maastricht VE Questionnaire. The items cover excessive fatigue, sleep problems (falling, waking up at night or unrested),  general discomfort, apathy, irritability, loss of energy, and demoralization; 18 is the highest score indicating severe exhaustion; furthermore, the Pearson *r* coefficient reported is 0.94 [46].

*Hospital Anxiety and Depression Scale* [HADS] [47]: this questionnaire assesses anxiety and depression symptom frequency and severity within the last week. It consists of 14 items building the two scales anxiety and depression. Both scales range from 0 to 21, have good validity, and report a Cronbach’s alpha of 0.80–0.81 [47].

*Fear Avoidance Beliefs Questionnaire* [FABQ-D], German version [48]: it consists of 16 items building 3 subscales (physical activity, work-related, and work prognosis) ranging from 0 to 30 [48]. A study on neck pain patients reports a Cronbach’s alpha of 0.90 [52].

*Berlin Social Support Scale* [BSSS] [27]: the questionnaire comprises six subscales regarding cognitive and behavioral social support aspects. Along, two main scales (perceived available and actually received social support) can be built. For both main scales, the internal consistency Cronbach’s alpha is 0.83 [27].

*Inventory of Life-Changing Events* [ILE] [49]: a total of 40 life-changing events are listed, in which participants can indicate whether they had already experienced such event and how often during the last 2 years. The number of a person’s life-changing events is analyzed as an accumulated number. In addition, in three of these events, the participant can indicate the subjective burden of the event by means of 10 extra questions. This score range from 0 to 48 points, a higher number means a higher burden. In a reliability study about the correlations between life events and diagnosed diseases, the instrument was judged as valid [49].

##### Patient compliance and acceptance

To measure patient compliance to the intervention program (therapy adherence), the frequency of sensorimotor training, patient education activities, and the use of body scan is registered in the training journal. This frequency may range from zero to three times weekly during 24 weeks. Further, the level of sensorimotor training difficulty is recorded as well as the degree of pain before and after exercises, using the 11-point *Numeric Rating Scale*. Additionally, a self-designed question “How often do you perform the aftercare exercises?” will be asked to all participants at T2 and T3 in order to have a subjective assessment of patient compliance.

The level of acceptance of the program will be assessed using self-developed question blocks (blocks represent the constructs defined through a factor analysis in the pilot study). The constructs are satisfaction with the program (it includes the questions “How satisfied are you with your aftercare program?” and “How do you rate the effect of the program you have completed?” from T2 and T3, Likert scale 0–10), self-competence acquired to continue with the program after the center-based rehabilitation stay (it consists of 8 questions from T1 such as: “How convinced are you that you will be able to use the learned exercises after the rehabilitation stay?”, “How well prepared do you feel with regard to time after rehabilitation stay?” and “How helpful did you find the preparatory exercises during rehabilitation stay?”, Likert scale 0–10), and sustainability (including “How confident are you that you will continue to use your aftercare program regularly?” from T2 and T3, Likert scale 0–10, and open questions as “What could stop you from continuing the exercises?”).

